### Informed Consent

Trained m2m program facilitators will collect informed consent from adults and informed assent from adolescents before the baseline at local schools in communities where the study is taking place (Multimedia Appendices 1 and 2). Informed consent and assent forms will include clear descriptions of the intervention, study objectives, use and protection measures for participant data, and participant rights to refuse to respond to survey questions or withdraw at any point from the study. Adolescents’ participation will be conditional on their parents providing consent. Adults and adolescents who agree to participate in the intervention will be invited to sign a paper-based informed consent form to indicate their consent. Participants will also receive a hard copy of information sheets, which include contact details of the local research team and ethics board.

### Additional Consent Provisions for Collection and Use of Participant Data

Parents and adolescents will be required to have provided informed consent to participate in the CHAMP project before recruitment to the study.

### Interventions

#### Intervention Description

The core parenting intervention component will be ParentText, a chatbot that delivers personalized and gamified scheduled and on-demand messages through text, audio, and visual media based on development stages for parents of children aged 0 to 23 months, 2 to 9 years, and 10 to 17 years. Previous research has reported the acceptability and feasibility of ParentText in LMICs. A qualitative formative research study in Jamaica reported an average participant (ie, parents) engagement length of 14 days throughout the 37 days of the intervention [43]. The version of the program targeting those aged 10 to 17 years will be used in this study in alignment with the age group of adolescent girls targeted by the CHAMP program. ParentText was originally developed by the UK-based charities PLH and Innovations in Development, Education, and the Mathematical Sciences (IDEMS) International in collaboration with the United Nations Children’s Fund (UNICEF); the Universities of Oxford and Cape Town; and Clowns Without Borders South Africa (CWBSA), one of the local partners, to ensure linguistic, cultural, and contextual relevance. The main program content was derived from the PLH for Parents and Teens program, a 14-session in-person intervention developed and tested in a cluster-randomized controlled trial in South Africa [55]. Additional content was included to support adolescent mental health (UNICEF’s Helping Adolescents Thrive program [56]), adolescent educational outcomes (the LEGO Foundation’s learning through play resources [57]), and gender-based violence prevention (No Means No Worldwide). All content was translated into isiZulu and siSwati and reviewed by parenting experts who were fluent in the 2 languages.

ParentText messages are grouped into nine positive parenting goals: (1) *improve my relationship with my teen*; (2) *understand teen development*; (3) *support my teen’s education*; (4) *create structure for my teen*; (5) *improve my family’s finances*; (6) *care for my teen’s well-being*; (7) *manage my teen’s behavior*; (8) *keep my teen safe*; and (9) *have a healthy relationship with my partner*, the latter only delivered to parents who have indicated that they are in a partnered relationship. Each goal is supported by learning modules (37 in total) designed to build parent interpersonal skills through comics, videos, and text illustrating key parenting tips. ParentText also includes internal components to support user engagement, such as gamification (eg, earning badges toward goals), personalization (eg, male and female videos), and activities (eg, quizzes). Participants can select the order of goals based on their preferences after completion of the first goal (*improve my relationship with my teen*).

The goal *improve my relationship with my teen* “improve my relationship with my teen” (Table 2) will provide content on how to spend one-on-one time with the teenager and techniques to praise the adolescent and talk about feelings. For the goal “understand teen development,” parents will complete modules related to understanding teenage mental, social, and physical changes. The goal “support my teen’s education” will deliver content related to creating a fun and positive environment to support the teenager’s academic learning process. Parents will learn skills to create a routine for teenagers and establish rules for the goal “creating a structure for my teen.” The goal “improve my family’s finances” will equip parents with budgeting skills through lessons related to savings and expenses. The goal “show kindness to your teen” will deliver content related to identifying and managing stress signs and techniques for supporting adolescents. For the goal “keep my teen safe,” parents will receive content related to building skills to manage teenagers’ misbehavior and help keep their adolescents safe in the community and relationships. Finally, parents who report being in a relationship will receive additional content on how to be supportive, solve conflicts in a relationship, and share responsibilities. The number of assigned modules will vary based on the age of the child and the number of goals but will be up to a total of 37, or 32 for nonpartnered parents.

Participants will be enrolled in the intervention for 6 weeks. Participants who enroll in the hybrid format of the program will also participate in 6 weekly WhatsApp live support sessions and 3 biweekly sessions of the in-person program subject to the study components available to their cluster. Parents will participate in the intervention by interacting with ParentText and completing each of the 37 modules and 9 goals sequentially. All goals and modules will be available to parents from the moment they enroll in the parenting chatbot. The goal “Have a Healthy Relationship with my Partner” will only be available for parents who reported being in a relationship. The order in which parents choose to access the goals will not be relevant because the goals were not developed to be interdependent. Adolescents will not interact with the chatbot but will experience the program through voluntary participation in the home practice activities of their parents.

The implementation will follow a group-based format that includes 3 joint parent-and-teenager sessions on (1) emotional check-in and mindfulness-based exercises to reduce stress, (2) feedback activity on participants’ experience with ParentText, (3) core lesson supported by illustrations, (4) collaborative discussion problem-solving, and (5) practice of skills at home. Participants will be trained on skills such as family budgeting, widening circles of support, and keeping safe in the community and in relationships. WhatsApp live chat group sessions will only include text messages. The session will include (1) a welcome and check-in message sent by the m2m facilitator, (2) sharing success (parents will be encouraged to share a positive experience when trying one of the ParentText skills with their teenagers), (3) fun activity that parents will be encouraged to replicate after with their teenagers (eg, a dance move), (4) sharing challenges (challenges faced by parents when trying a new skill with their child), and (5) collaborative discussion problem-solving.

**Table 2 table2:** Intervention modules—ParentText content.

Goal	Number of modules	Justification
Improve my relationship with my teenager	3	A stronger parent-child relationship is associated with lower levels of conflict and violence in families [58].
Understand teenager development	3	Parents who understand the development of an adolescent’s sexual and reproductive health are better equipped to create a safe and supportive environment for them. Parental monitoring, communication, and support are vital in sexual violence and VAC^a^ prevention [59].
Support my teenager’s education	5	Research suggests that parents who are involved in their adolescents’ education help provide a positive school environment by promoting the love for learning [60].
Create structure for my teenager	4	Rulemaking can decrease disputes between parents and their children. When parents set rules, they can protect their children from harmful acts or behaviors that may result in abuse by other adults [61].
Manage my teenager’s behavior	4	Managing adolescents’ behavior prevents later involvement in risky behavior, such as substance use, violence, later delinquency, and conduct problems [62].
Care for my teenager’s well-being	4	Listening actively helps adolescents feel heard, understood, less alone, and calmer. In contrast, if parents do not listen to and support their adolescents properly, this can leave them feeling defensive, frustrated, alone, or hurt [63].
Keep my teenager safe	4	Adolescents are at a higher risk of becoming victims of crime than any other age group [64].
Have a healthy relationship with my partner	5	Fatherhood programs that encourage fathers to be more engaged in caregiving and parenting show hopeful findings in terms of reducing VAC and IPV^b^ [65].
Improve my family’s finances	4	According to the family stress model, financial problems increase parents’ stress and depression, which in turn increases harsh parenting practices and child maltreatment [66].

^a^VAC: violence against children.

^b^IPV: intimate partner violence.

#### Tested Intervention Components

##### Intervention Component 1: In-Person Sessions

This trial will examine whether varying frequency of in-person human support significantly affects user engagement with the chatbot. In-person parenting programs come with the costs of training facilitators and commonly present limited community resources and infrastructure for their delivery [21]. Of the variants of human support selected for this trial, the in-person component requires a greater allocation of resources. Nevertheless, there is great value in understanding how much of the in-person component is necessary to bolster engagement in chatbot-led public health interventions. Proponents of remote support tools argue that including social networking as a tool to support participants is associated with greater engagement rates [67,68]. In supported digital interventions, participants receive technical and clinical troubleshooting assistance to bolster engagement [69]. Previous studies have reported that the frequency with which participants interacted with a counselor or clinician coach predicted their adherence to digital health interventions [67,70].

This study will compare the differential effects of delivering either 1 or 4 in-person group-based sessions to parents and their adolescents (maximum of 60 families per group). Each session will be delivered by an m2m CHAMP lead facilitator and a cofacilitator and last approximately 2 hours.

##### Intervention Component 2: Facilitated WhatsApp Support Groups

This study will also test the impact of facilitated WhatsApp support groups on user engagement in the ParentText chatbot intervention. Self-guided interventions present greater scope for scalability due to the low allocation of financial and human resources required. However, low engagement rates risk their sustainability over time. Although including engagement boosters is a common practice in parenting programs to increase parent engagement [53,54], their effectiveness in increasing engagement has been challenged in previous studies. Day and Sanders [71] found that parents benefited from phone support when completing the Triple P Online self-guided parenting program. Parents in the practitioner-supported condition engaged more with the program, completing more modules and reporting greater program satisfaction [71]. However, Epstein et al [72] found that providing opportunities for parents to interact via Facebook groups while participating in a self-directed family intervention did not increase engagement or improve parenting practices.

In this study, 6 one-hour WhatsApp support groups will be delivered to participating parents (maximum of 60 participants) by a trained m2m CHAMP facilitator. The facilitator will lead and monitor discussions and respond to any questions parents raise about technical troubleshooting and the content of the chatbot. At the end of the fifth WhatsApp group session, participants will be asked to select 2 peer leaders who will assume the responsibility of moderating the group after the sixth session.

As shown in Figure 1, the study components will contribute to increased engagement rates (eg, the number of modules and home practice activities completed within the parenting chatbot) among participants. Higher engagement rates will lead to more positive parenting practices and parent-teenager relationships, resulting in improved mental health and education outcomes for teenagers. Engagement with the chatbot will also contribute to improved intimate partner relationships and lead to positive mental health outcomes for parents. The sustainment of proximal outcomes will lead to a healthier environment within the household and contribute to reduced VAC and improved child learning outcomes.

**Figure 1 figure1:**
[figure not shown]
ParentText Optimisation Trial conceptual model.

### Training of Facilitators

m2m staff will be trained as program facilitators by certified trainers from CWBSA, a South African NGO with vast expertise in leading PLH program training. Training will occur over 2 days lasting a total of 12 hours. In total, 4 separate intervention manuals were developed to create a standardized delivery of the sessions based on condition allocation (ParentText+onboarding; ParentText+onboarding+WhatsApp support group; ParentText+onboarding+WhatsApp support group+3 in-person sessions; ParentText+onboarding+3 in-person sessions).

### Criteria for Discontinuing or Modifying Allocated Interventions

Adult and adolescent participants will have the right to decline any assessment or participation at any time during the study. Participants can opt out of receiving ParentText messages at any point by typing “EXIT” or simply by not responding to the messages. The decision to withdraw from the study will not affect a participant’s entitlement to other services or result in any penalty. Data collected through paper-based surveys and in-built assessments will be retained unless participants request otherwise.

### Strategies to Improve Adherence to the Intervention

Internet bundles (50 ZAR [approximately US $2.60] per person) will also be provided to support engagement with ParentText regardless of intervention condition allocation. Additional data bundles will also be provided to those allocated to participate in WhatsApp support groups.

### Relevant Concomitant Care Permitted or Prohibited During the Trial

Participants will not be prevented from receiving other care or services during the trial period.

### Provisions for Posttrial Care

Safeguarding procedures will be used to mitigate risks to participants. There is a possibility of participants disclosing violent practices toward their children, their partners, or themselves. The informed consent form indicates that some information regarding harmful behaviors will be disclosed without the participant’s consent if they pose a danger or harm to themselves or their family members. Participants at risk will be referred to local child welfare, health organizations, and other social services. Building on UNICEF’s safeguarding guidelines, ParentText has been designed to recognize high-risk keywords such as “trouble,” “SOS,” “ill,” “anxiety,” and “fire” in free-text fields. Participants can also type “HELP” to receive troubleshooting messages. The chatbot will respond to participants’ disclosure of dangerous situations automatically in an empathetic and empowering manner. It will also provide referral contacts localized in Mpumalanga to offer support to participants who are in danger of being harmed. All supporting services available for participants were identified by m2m and implementing teams following a meticulous mapping of local governmental and nongovernmental support systems. Finally, if respondents or their families are determined to have experienced significant harm because of participating in the study (ie, severe abuse, suicidality, IPV, or other potential psychological or physical injuries), we will cease further activities until these issues can be addressed adequately.

### Outcomes

Primary and secondary engagement outcomes will be collected through the course of the program implementation from August 21, 2023, to September 8, 2023.

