#### Primary Outcomes: Engagement

The primary outcome related to user engagement is defined as the overall number of modules completed within the ParentText chatbot.

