#### Secondary Outcomes

##### Engagement Outcomes

Secondary engagement outcomes will include the percentage of modules and goals completed. We will also examine the rate of self-reported completion of home practice activities based on the self-reported intention to do home practice activities. In total, 3 home practice activities will involve actual interaction with the chatbot, which will allow for testing whether users lie about completing home activities when prompted. Additional engagement outcomes will include the number of days users interact with the chatbot, number of triggered safeguarding messages, number of active and passive dropout from the chatbot, number of times users use the menu and option functions, number of times users access learning through play activities and type of activity (ie, calm, active, quick, or group), type of media selected for engagement (ie, text, audio, or video), and goal selected by users after completion of the first goal. For participants in all clusters, we will compute sum scores for each engagement outcome measure for the complete study period. High engagement rates will be defined as values standing at the highest quartile of the averaged engagement score, medium engagement rates will be defined as values at the second or third quartile, and low engagement rates will be defined as values at the lowest quartile.

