### Participant Timeline

The participant timeline is summarized in Figure 2. Sampling will be purposive and integrated into m2m CHAMP’s current recruitment strategy for the DREAMS project component. Recruitment will proceed until 60 parent-adolescent dyads per cluster are enrolled. Adult and adolescent participants will then be invited to an in-person session that will include (1) informed consent, (2) baseline assessment, (3) onboarding session, and (4) intention to use and cultural determinant survey (August 21, 2023, to September 8, 2023). Parents who complete the baseline assessment will receive a WhatsApp link to connect with ParentText and receive guidance on how to interact with the chatbot. The onboarding session will also include end-to-end testing to ensure that the chatbot functions correctly. Participants will be invited to interact with the chatbot for 5 minutes simulating a real-world interaction. They will then be asked to complete a paper-based assessment to collect their behavioral intention to use ParentText and cultural determinants. Depending on their assignment condition, parents will also be invited to join a facilitated WhatsApp support group or attend additional in-person sessions with their adolescent girls. The ParentText messages will be sent daily to parents via WhatsApp regardless of assignment condition. Data collectors will conduct posttest assessments approximately 6 weeks after the baseline (October 8-27, 2023). Follow-up assessments beyond the postintervention end point will not be conducted.

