### Trial Status

Recruitment for the ParentText Optimisation Trial will begin on August 21, 2023, and is anticipated to continue until September 8, 2023. Baseline data collection will start on August 21, 2023, and is expected to be completed by September 8, 2023. This is the protocol version [1] of August 22, 2023.

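### The only dates given for collecting the primary engagement outcome are those of recruitment, baseline and onboarding, which contradicts the 6-week programme and leaves the counting window undefined

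*Protocol article*

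**What the plan says.** All references are to the protocol article.

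- **Primary Outcomes: Engagement** defines the outcome without a time window: "The primary outcome related to user engagement is defined as the overall number of modules completed within the ParentText chatbot".
- **Outcomes**, immediately before it, supplies the only dates: "Primary and secondary engagement outcomes will be collected through the course of the program implementation from August 21, 2023, to September 8, 2023".
- **Trial Status** gives the same dates for two other activities: "Recruitment for the ParentText Optimisation Trial will begin on August 21, 2023, and is anticipated to continue until September 8, 2023" and "Baseline data collection will start on August 21, 2023, and is expected to be completed by September 8, 2023".
- **Participant Timeline** gives them again for the session that covers consent, baseline, onboarding and the last listed step, "4) intention to use and cultural determinant survey (August 21, 2023, to September 8, 2023". Chatbot access starts there: "Parents who complete the baseline assessment will receive a WhatsApp link to connect with ParentText". The same section puts posttest on October 8-27, 2023.
- **Intervention Description** sets the length of the programme: "Participants will be enrolled in the intervention for 6 weeks". It schedules six weekly WhatsApp sessions and three biweekly in-person sessions in the conditions that have them.
- **Trial Design, Overview** runs the trial from August 21 to November 10, 2023.
- **Secondary Outcomes, Engagement Outcomes** gives a different scoring period: "we will compute sum scores for each engagement outcome measure for the complete study period". That period is not defined.

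**The concern.** One sentence calls August 21 to September 8 the course of implementation. Every other section treats those dates as the intake period, in which parents are recruited, assessed and given access to the chatbot. A programme that starts for each parent at some point in those 19 days, and then lasts 6 weeks, cannot be observed within them.

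The primary outcome is a count, so the period over which it is counted is part of its definition. As written, an analyst has one dated window that is too short and one undated window that is undefined, and nothing in the article says which governs.

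Much rests on this count. The section on selecting the optimal package screens components in or out on their main effects on primary engagement. The cost-effectiveness analysis uses the same module count. Engagement quartiles also guide the choice of interviewees.

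**Working it through.** **Inputs.** Stated collection window: August 21 to September 8, 2023 (Outcomes). Onboarding window: the same dates (Participant Timeline). Programme length: 6 weeks = 42 days (Intervention Description). Posttest: October 8-27 (Participant Timeline). End of trial: November 10 (Trial Design).

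**Plan's own figure.** The article's only calculated design figure is the minimum detectable effect. With 16 clusters of 60 parents per component level and SD 1, (1.645 + 0.842) × √(2 × (1 + 59 × 0.02) / (16 × 60)) = 0.168, which matches the Sample Size section. It contains no time window, so it neither helps nor harms here.

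**Length of the stated window.** September 8 − August 21 = 18 elapsed days, or 19 counting both ends. That is 18/42 = 43% to 19/42 = 45% of the programme. It closes 30 days before posttest opens (October 8 − September 8).

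**Days captured if the dates are applied literally** (September 8 − onboarding date; add 1 for the inclusive count):

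| Onboarded | Elapsed days | Inclusive days | Share of 42 days |
|---|---|---|---|
| August 21 | 18 | 19 | 43-45% |
| August 30 | 9 | 10 | 21-24% |
| September 8 | 0 | 1 | 0-2% |

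If onboarding is spread evenly over the window (an assumption, since the article gives no distribution), the mean is 9 to 10 days: 9/42 = 21% to 10/42 = 24%. At least 1 − 19/42 = 55% of the programme falls outside the window for every parent.

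**Sessions delivered by then, for the earliest parent.** Assume sessions run from that parent's onboarding. Weekly WhatsApp sessions on days 7 and 14, or on days 1, 8 and 15, give 2 to 3 of 6. Biweekly in-person sessions starting two weeks after onboarding give about 1 of 3, because the next falls on day 28. Later parents would have had fewer.

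**A 42-day window per parent.** From August 21 it ends on October 1 (onboarding day counted as day 1) or October 2 (elapsed days). From September 8 it ends on October 19 or 20. Both ends lie within the trial period, and the later one falls inside the posttest window.

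**The case against.** The best defence is that this is a slip in a date and not the plan. The sentence itself speaks of the whole course of implementation. The primary outcome is an overall count with no cut-off. Engagement is elsewhere scored over the complete study period, and the abstract reports that data collection was finalised in November 2023. Only the date string points to truncation, and it matches the intake dates so exactly that copying is the likely explanation. This stands: a reader might infer that the trial means to stop counting on September 8, and the article as a whole does not support that.

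The defence is also right about size. Days are not modules. All modules are open from enrolment, the Introduction cites higher dropout after 2 weeks, and an earlier ParentText study found an average engagement of 14 out of 37 days. Losing about three quarters of the days therefore need not lose three quarters of the completed modules. A reader might infer that both main effects would be biased toward zero. That is plausible for a difference in counts, but it is not established for the rate ratio from a Poisson model, which truncation could leave unchanged or move either way.

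Three further inferences should not be drawn:

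- **A common cut-off on November 10.** The article does not say that the complete study period means this. Read with the 6-week enrolment, it could equally mean about 42 days per parent.
- **A missing exposure offset.** This is model detail that an analysis plan may hold.
- **Imbalance between conditions in onboarding dates.** No dates by cluster or condition are given, and allocation is randomised.

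What the defence does not remove is the contradiction. The only dates attached to the primary outcome are wrong for a 6-week programme, and no other passage corrects them.

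**Conclusion.** The point holds as an internal contradiction in the definition of the primary outcome, to be corrected before the engagement data are analysed. The stated dates conflict with the 6-week programme, the October posttest, the trial period and the undefined complete study period. The most likely cause is that the recruitment dates were carried over.

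The size is conditional on applying the sentence literally: 18-19 of 42 days at most, 0-1 at least, and a mean of about 21-24% if onboarding is uniform. Most of the sessions that distinguish the conditions would then come after counting had stopped, so the component contrasts could be distorted. The direction and amount of distortion on the model's scale cannot be derived from the article. The arithmetic rests on calendar dates in the article, on the counting convention (both are shown), and on sessions being timed from onboarding.

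**What to change.** Correct the dates in the Outcomes section, and define the complete study period under Engagement Outcomes in the same terms. Suggested wording: *Each engagement outcome is counted for each parent from the day of that parent's onboarding (day 1) through day 42.* With this convention the last window closes on October 19, 2023 (October 20 if elapsed days are used). State which convention applies.

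One fixed window per parent settles the contradiction and gives every parent equal exposure whatever the onboarding date.

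The cost is a change of wording in two places and one date filter. Chatbot engagement is tracked digitally and stored automatically. Because days of interaction is itself a listed outcome, the log should carry the dates that the filter needs. No new data collection is involved.
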